## Background of the Project including Preliminary Observations

Describe the relevant background of the proposed study. Discuss the previous related works on the subject by citing specific references. Describe logically how the present hypothesis is supported by the relevant background observations including any preliminary results that may be available. Critically analyze available knowledge in the field of the proposed study and discuss the questions and gaps in the knowledge that need to be fulfilled to achieve the proposed goals. Provide scientific validity of the hypothesis on the basis of background information. If there is no sufficient information on the subject, indicate the need to develop new knowledge. Also include the significance and rationale of the proposed work by specifically discussing how these accomplishments will bring benefit to human health in relation to biomedical, social, and environmental perspectives.

Zinc deficiency has been found to be widespread among children in developing countries, occurring throughout Latin America, Africa, the Middle East and South Asia. It has been estimated that the annual Disability Adjusted Life Years (DALYs) lost due to zinc deficiency is over 57 million (1) . Children between 6 months to 5 years of age who receive zinc for the treatment of a diarrheal illness (20 mg/day for 10 days) recover faster, have a 30% reduction in the likelihood of developing prolonged diarrhea, and have an estimated 50% reduction in non-injury mortality over the next 6 months (2-8). In response to this evidence, WHO/UNICEF revised its childhood diarrhea management recommendations to include zinc in the treatment of any under-five child with a diarrheal illness (9). This evidence also sstimulated the develpoment of the Gates Foundation funded Scale Up of Zinc for Young Chuildren (SUZY) Project. The SUZY Project is now into its fourth and final year. The national roll-out of a zinc providedr promotion and mass media campaign in support of “baby zinc” is scheduled to begin in late September or early October, 2006.

As part of the Project monitoring plan a baseline national survey of childhood diarrhea management practices was carried out in 2004. Stratified by rural, urban and city corporation slum and non-slum populations, the aims of that survey were to document help seeking practices, treatments given, and illness expenditures. An important issue that the baseline survey and this follow-up survey addresses is that of equity. Most new health interventions are preferentially used by the more well-to-do, with the poor excluded and lacking access to new technologies. This project intends to monitor for the inequities (e.g. by gender and income) and provide guidance for pro-poor policy and programming decisions. Special efforts have been made to tailor media messages for the poor.

The baseline survey documented that throughout Bangladesh health seeking behaviors for childhood diarrhea are dominated by utilization of private sector providers (10). It is evident that unlicensed providers, whether “village doctors”, drug sellers or homeopaths, continue to be the preferred source of care, in particular among the rural poor. It was also found that significant variation in the type of provider seen occurs by where the child lived. In Bangladesh licensed providers are predominantly allopathic doctors (MBBS), while unlicensed providers are typically individuals with minimal or no formal training who imitate the prescribing patterns of trained, qualified doctors. Unlicensed providers (allopaths, drug sellers, homeopaths) were visited in over 90% of rural and over 75% of inner-city slum cases when care was sought. Unexpectedly, it was found that urban, non-slum when compared to poorer rural and slum households, were twice as likely to seek services from the public sector.

Disparities on the basis of income in care seeking behavior were identified in rural and urban populations. This was true for any provider as well as for a licensed allopath with significant trends (p<.001) favoring higher income households occurring throughout Bangladesh. When adjusted for host and illness characteristics, within urban households the most consistent predictors for seeing a licensed allopath were higher income, longer duration of illness and higher education of mothers. In rural households, where access to licensed providers is much more restricted, the most important predictors were younger age of child, longer duration of illness and mothers’ education. Gender disparites in provider utilization were not identified among rural households. When comparing female to male children, the crude estimates for seeking help from any provider or a licensed allopath favored males from city corporation, non-slum households. These disparities disappeared when the analysis was adjusted for other predictors of utilization. In contrast, within urban municipal households females were found to be 30% less likely to have been seen by a licensed allopath. No gender bias for provider utilization (licensed or unlicensed) was identified among the much poorer inner-city slum households.

With respect to total direct expenditures on a diarrheal illness, there was a consistent trend across all locations to spend more on male children, however this only reached statistical significance among city corporation, non-slum households. A similar trend was found for purchase of an antibiotic and may explain the expenditure disparities. Receipt of an antibiotic is closely correlated with having seen a provider and therefore these two outcomes will share similar predictors. This included higher income and maternal education, longer duration of illness, and younger age. An additional predictor of antibiotic use, as would be desired, was the finding that children with bloody diarrhea were twice as likely to receive an antibiotic.

The treatment protocol to be scaled up in Bangladesh is a 10 day course of 20 mg of zinc daily provided in either a dispersible tablet or syrup formulation. The tablets are converted from a solid tablet to a syrup with the addition of a few drops of water. The tablets will be packaged and sold in a 10 tablet blister pack. The choice of a 10 day treatment protocol is based upon expectations regarding the expected length of compliance (to be monitored) and current production capacities, which are set to produce 10 tablet blister packs.

The SUZY Project has already completed a great deal of provider promotion that has addressed zinc treatment of childhood diarrhea generically. Nearly all licensed and probably most unlicensed providers are aware of zinc as a treatment for childhood diarrhea and many are prescribing it. Thus, one purpose of this proposed follow-up survey ,in its first of three rounds, is to establish the post-provider promotion, but pre mass media coverage of zinc and to then monitor for change in diarrhea management practices as the Baby Zinc roll-out campaign is implemented. Equally important will be the monitoring of ORS and zinc use. Both outcomes will be stratified by income status, gender of child and location of residence.

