Appendix 5: Detailed Budget

Appendix 6: Questionnaire

[Check-List](#__RefHeading___Toc132346870)

Check here if appendix is included

| Project Summary Describe in concise terms, the hypothesis, objectives, and the relevant background of the project. Also describe concisely the experimental design and research methods for achieving the objectives. This description will serve as a succinct and precise and accurate description of the proposed research is required. This summary must be understandable and interpretable when removed from the main application. **(Please keep as brief as possible).** |
| --- |
| Principal Investigator(s): [name] |
| Research Protocol Title: Monitoring the Impact of the SUZY Project role-out of Zinc as a Treatment for Childhood Diarrhea |
| Total Budget US$: 208,423 Beginning Date : 01/09/06 Ending Date: 15/06/07 |
| This is a repeat, ecologic survey to document changes in zinc coverage for childhood diarrhea, coinciding with the national roll-out of “Baby Zinc”. The surveys have been stratified by location; rural, urban municipalities, and city coprportation slum and non-slum populations.  In addition to zinc coverage, the surveys will monitor changes in the use of ORS or antibiotics, expenditures on diarrheal illnesses and other management practices. The surveys have been powered to identify disparities in care based upon gender, income and location of households.  The survey field sites have been purposively selected in order to facilitate comparisons with the baseline national coverage survey carried out in 2003/4. These include rural upazilla (Mirsarai, Abhoynagar, Hobiganj), urban municipalities (Khulna, Sylhet, Camila), and City Corporation zones (slum: kamalapur, Mirpur and non-slum Green--------- The same interviewer administered questionnaire will be used.  The results of this study will provide guidance for public, private and NGO delivery systems as they jointly endeavor to reach all under-five children with zinc treatment of any diarrheal disease episode. |
| KEY PERSONNEL (List names of all investigators including PI and their respective specialties)     | Name | Professional Discipline/ Specialty | Role in the Project | | --- | --- | --- | | 1. [name] | Health services research | PI | | 1. [name] | Statistician | analyses, data management | | 1. [name] | Field studies | Coordination of survey conduct | |

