## Research Design and Methods

Describe in detail the methods and procedures that will be used to accomplish the objectives and specific aims of the project. Discuss the alternative methods that are available and justify the use of the method proposed in the study. Justify the scientific validity of the methodological approach (biomedical, social, or environmental) as an investigation tool to achieve the specific aims. Discuss the limitations and difficulties of the proposed procedures and sufficiently justify the use of them. Discuss the ethical issues related to biomedical and social research for employing special procedures, such as invasive procedures in sick children, use of isotopes or any other hazardous materials, or social questionnaires relating to individual privacy. Point out safety procedures to be observed for protection of individuals during any situations or materials that may be injurious to human health. The methodology section should be sufficiently descriptive to allow the reviewers to make valid and unambiguous assessment of the project.

Study design: A repeat, ecologic survey in three rural upazillas, three municipalities and two city coprporation slum plus two non-slum zones is proposed. The survey team will complete three survey cycles per site, each cycle estimated to require 10 weeks to complete. The surveys will be carried out from September, 2006 through April, 2007 (SUZY Project funding ends in June, 2007).

Survey Populations

a. Rural: The sub-districts of Mirsarai, Abhoynagar and Hobiganj have been purposively selected. Within

each sub-district we will randomly select 20 clusters based upon a listing of all wards in the subdistrict.

All wards will be enumerated and then randomly selected.

b. Urban: The district municipalities of Khulna, Camila and Sylhet have been purposively selected. Twenty

clusters will be randomly selected within each municipality. Clusters are defined as geographic units

(“strata”) within the municipality that will be enumerated.

c. Dhaka City Corporation: slum zones of Kamalapur and Mirpur, non-slum zones (and wards) of Green

Road and Old Dhaka. Within each zone 20 clusters will be selected. Clusters are geographically defined

population“units” based upon the most recent census

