Within each cluster a household census survey will be completed for the identification of any under -five child who has had a diarrheal ilness in the past two weeks of at least 2 days duration. The aim is to identify 16 cases per cluster.

Within each site, random cluster selection will be repeated at the time of each new survey round. The sampling framework is summarized in figure 1.

CHILDREN UNDER FIVE YEARS OF AGE

Diarrheal Disease Episode in past 2 weeks and

at least 48 hrs duration

Dhaka Urban Municipalities Rural Upazillas

2 slum zones Khulna Abhoynagar

2 non-slum zones Camila Mirsarai

Sylhet Hobiganj

random random random

20 clusters 20 clusters 20 clusters

per zone per municipality per upazilla

at 16 casesper cluster

n=320 cases per site

N= 640 slum N=960 N=960

N= 640 non-slum urban municipal rural cases

per round per round per round

Figure 1. Summary of sampling frame for cluster surveys

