## Sample Size Calculation and Outcome Variable(s)

For each survey round (weeks 1 to10, 12 to 21 , 23 to 32 weeks) we are determining estimates of zinc, ORS and antibiotic use (prevalence). With each new interval we will be sampling from the same sites, but will carry out a new random selection of clusters in which cases will be identified.

As depicted in figure 1, for each survey round the number of subjects by site and location is as follows:

Location Sites N/site N/location

City corporations Slums x 2 320 640

Non-slums x 2 320 640

Urban Municipalities x 3 320 960

Rural Upazillas x 3 320 960

Based upon WHO EPI cluster survey methods, the design effect is estimated to be 2.0 (11)

a. Prevalence of zinc treatment by site: Setting confidence at 0.95 and a minimal detectable error of a 5% for a prevalence estimate within a site, assuming the baseline overall prevalence of zinc coverage to be 10%:

(Z alpha )2 (P)(1-P)

N/site = x 2 (cluster adjustment design effect)

d 2

N/site = 276 cases

b. Trends in use of ORS and antibiotics by site: Setting confidence at 0.95 and a minimal detectable error of 10% around a prevalence of 50% of cases being treated with ORS or an antibiotic;

N/site = 198

d. Comparison of two proportions (hypothesis testing):

To examine whether zinc coverage in urban or rural locations is significantly different among males vs females, setting the level of conficence at .95 (one-sided), power at .80, minimal detectable difference 10%, assuming an overall prevalence of 25% coverage by the third cycle

(Z alpha + Z beta)2 (P)(P-1) x 2

N/gender/location = x 2 (cluster adjustment design effect)

d 2

N/location = 461

Given these estimates, we will have the power to detect smaller differences in the rural and municipality

locations. In the City Corporations sites the power is adequate if we combine slum and non-slum populations. Keeping them separate will allow for a minimal detectable difference of 12%.

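### Round 1 is meant to give zinc coverage before mass media, but on the protocol's own dates the campaign starts before round 1 ends, so round 1 as a whole cannot serve as a pre-media baseline

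*Protocol*

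**What the plan says.** The last paragraph of the Background gives round 1 a specific task: one purpose of the survey, in the first of three rounds, "is to establish the post-provider promotion, but pre mass media coverage of zinc". Later rounds then follow change as the campaign is implemented.

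Earlier in the Background, the national roll-out, described as provider promotion together with mass media, "is scheduled to begin in late September or early October, 2006". No separate date is given for mass media.

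The timetable is set in three places:
- Project Summary: "Beginning Date : 01/09/06 Ending Date: 15/06/07".
- Research Design and Methods: "The surveys will be carried out from September, 2006 through April, 2007", with "each cycle estimated to require 10 weeks to complete".
- Sample Size Calculation: "For each survey round (weeks 1 to10, 12 to 21 , 23 to 32 weeks", so round 1 is weeks 1 to 10.

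A case is an under-five child who "has had a diarrheal ilness in the past two weeks of at least 2 days duration". The sample size section assumes zinc coverage of 10% at baseline and 25% by the third cycle. H1 expects an upward trend in zinc use over eight months, and H2 a downward trend in antibiotic use for non-bloody diarrhoea.

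**The concern.** Round 1 has a label that its calendar cannot support. A ten-week round that begins in September is still running when a campaign due around the start of October is launched. Nothing in the protocol makes launch wait for round 1 to finish, and nothing separates round-1 cases by date relative to launch.

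Two things are at stake. The first is the pre-media coverage figure itself, which cannot be collected once the campaign is running. The second is the size of the change measured from it: if the campaign raises zinc use, post-launch cases lift the round-1 figure and shrink the apparent rise. The national survey of 2003/4 is a baseline of a different kind. The Background wants coverage after provider promotion and before mass media, and it does not describe the earlier survey in those terms.

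**Working it through.** **Inputs from the protocol.** Round 1 lasts 10 weeks (70 days); rounds are weeks 1–10, 12–21 and 23–32; recall is two weeks; coverage is 10% at baseline and 25% by cycle 3; design effect 2; 320 cases per site, 10 sites, 3,200 per round.

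**Assumptions.** Fieldwork starts on 1 September 2006 (this is the project start; for the surveys only the month is given). Launch falls between 20 September and 10 October. Interviewing runs at an even pace.

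**The plan's own figure.** N per site = 1.96² × 0.10 × 0.90 / 0.05² × 2 = 276.6; the protocol states 276. It reproduces.

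**Overlap.** Round 1 runs from 1 September to 9 November. The strict count drops the first 14 post-launch days, leaving only interviews whose whole recall window is after launch.

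| Launch | Days before | Days after | Share after | Whole recall window after |
|---|---|---|---|---|
| 20 Sep | 19 | 51 | 51/70 = 73% | 37/70 = 53% |
| 1 Oct | 30 | 40 | 40/70 = 57% | 26/70 = 37% |
| 10 Oct | 39 | 31 | 31/70 = 44% | 17/70 = 24% |

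Moving the earliest launch to 21 September changes the top row to 50/70 = 71% and 36/70 = 51%. A later fieldwork start makes the overlap larger. The latest start that fits 32 weeks before the end of April is 18 September, which puts 48/70 = 69% (launch 10 October) to 68/70 = 97% (launch 20 September) after launch. From 1 September, a wholly pre-media round 1 would need launch on or after 10 November.

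**Effect on the rise, by speed of uptake.** The protocol gives no uptake curve, so this is a range. The true rise is 25 − 10 = 15 points, and f is the share of round 1 after launch, counted by interview date.

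- *Gradual.* Coverage climbs linearly from 10% at launch (L weeks after the start) to 25% at mid-round 3 (27 weeks after the start). Excess in round 1 = 15 × (10 − L)² / [2 × 10 × (27 − L)]. For launch on 20 September (L = 2.71): 15 × 53.1 / 485.7 = 1.6 points. For 10 October (L = 5.57): 15 × 19.6 / 428.6 = 0.7 points. The measured rise is 13.4 to 14.3 points.
- *Intermediate.* Average post-launch coverage within round 1 of 12.5% to 20%. Round 1 reads 10 + 0.443 × 2.5 = 11.1% at the low end and 10 + 0.729 × 10 = 17.3% at the high end. The measured rise is 13.9 to 7.7 points. For a single-site comparison of rounds 1 and 3 (effective n = 320/2 = 160, two-sided 0.05), power falls from about 95% to between about 90% and 39%.
- *Immediate step to 25%.* For launch on 1 October: 10 + 0.571 × 15 = 18.6%, a rise of 6.4 points. With onsets spread evenly over the recall window, the post-launch share is (40 − 7)/70 = 47% and round 1 reads 17.1%. For each launch date this case is only an upper bound.

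**Size of a pre-launch-only baseline** (by interview date; half-width = 1.96 × √(2 × 0.09/n)).

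| Level | Full round | Launch 20 Sep | Launch 10 Oct |
|---|---|---|---|
| Site | 320 | 87 (±8.9) | 178 (±6.2) |
| Location of 640 | 640 | 174 (±6.3) | 357 (±4.4) |
| Location of 960 | 960 | 261 (±5.2) | 535 (±3.6) |
| All sites | 3,200 | 869 (±2.8) | 1,783 (±2.0) |

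Half-widths are in points.

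**The case against.** The strongest reply is that H1 is a trend over eight months, not a contrast before and after mass media. A trend across three rounds can survive partial contamination of the first, and the pre-media estimate is only one purpose of the survey. That stands: H1 remains testable, though the slope is attenuated if the campaign works. It does not rescue the pre-media estimate, which the protocol assigns to round 1.

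Recall also helps the plan, since interviews soon after launch often concern earlier episodes. This lowers the exposed share but does not remove it.

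Mass media might start later than the rest of the roll-out. That would reduce the overlap, but the protocol gives a single date for both.

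Three stronger readings are tempting and are not supported:
- That the rise will be more than halved. This needs coverage to reach 25% on launch day, whereas the sample size section expects that level only by the third cycle.
- That the analysis uses round number as its time variable. The Data Analysis section names no time variable, and that choice may properly sit in an analysis plan not seen here.
- That location disparities under H3 are confounded with visit date. This would need teams to visit sites in sequence, and the order of visits is not stated. Gender and income contrasts are examined within location, and the powered gender comparison assumes third-cycle coverage.

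**Conclusion.** The point holds as a conflict between the stated purpose of round 1 and the protocol's dates. It does not depend on the exact day of launch or of the September start. The 44% to 73% exposed share does depend on those assumed days and on even interviewing.

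The direction of bias assumes that the campaign raises zinc use, as H1 does. Its size cannot be fixed from the document. The gradual case, with a loss of 0.7 to 1.6 of 15 points, is closest to the protocol's own expectation and is smaller than the 5-point site precision that the protocol accepts. Faster uptake would cost several points. The firm conclusion is that round 1 as a whole must not be reported as pre-media coverage. A severe loss of the measured rise is possible but not shown.

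**What to change.** 1. Record episode onset and interview dates for every case, and the actual launch date.
2. Classify round-1 cases as before or after launch. Use only pre-launch episodes for the pre-media estimate, and state in advance how episodes that straddle launch are classed.
3. Include time relative to launch in the H1 and H2 trend models.
4. Keep the full round-1 estimate as well, labelled as spanning the launch.
5. If teams visit sites in sequence, order round 1 as far as feasible so that each of the four locations contributes pre-launch cases. This has to be settled before fieldwork, because later analysis cannot supply it.

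The data cost is two dates per case. The statistical cost is real: about 870 to 1,780 pre-launch cases in all, or 87 to 178 per site against the 276 that the protocol requires. The 5-point site precision therefore does not apply to the pre-media estimate, which should be reported pooled or by location with its own interval. With an early launch and sequential visits, some sites may have no pre-launch cases, and the report should say so.

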## Research Design and Methods

Describe in detail the methods and procedures that will be used to accomplish the objectives and specific aims of the project. Discuss the alternative methods that are available and justify the use of the method proposed in the study. Justify the scientific validity of the methodological approach (biomedical, social, or environmental) as an investigation tool to achieve the specific aims. Discuss the limitations and difficulties of the proposed procedures and sufficiently justify the use of them. Discuss the ethical issues related to biomedical and social research for employing special procedures, such as invasive procedures in sick children, use of isotopes or any other hazardous materials, or social questionnaires relating to individual privacy. Point out safety procedures to be observed for protection of individuals during any situations or materials that may be injurious to human health. The methodology section should be sufficiently descriptive to allow the reviewers to make valid and unambiguous assessment of the project.

Study design: A repeat, ecologic survey in three rural upazillas, three municipalities and two city coprporation slum plus two non-slum zones is proposed. The survey team will complete three survey cycles per site, each cycle estimated to require 10 weeks to complete. The surveys will be carried out from September, 2006 through April, 2007 (SUZY Project funding ends in June, 2007).

Survey Populations

a. Rural: The sub-districts of Mirsarai, Abhoynagar and Hobiganj have been purposively selected. Within

each sub-district we will randomly select 20 clusters based upon a listing of all wards in the subdistrict.

All wards will be enumerated and then randomly selected.

b. Urban: The district municipalities of Khulna, Camila and Sylhet have been purposively selected. Twenty

clusters will be randomly selected within each municipality. Clusters are defined as geographic units

(“strata”) within the municipality that will be enumerated.

c. Dhaka City Corporation: slum zones of Kamalapur and Mirpur, non-slum zones (and wards) of Green

Road and Old Dhaka. Within each zone 20 clusters will be selected. Clusters are geographically defined

population“units” based upon the most recent census

Within each cluster a household census survey will be completed for the identification of any under -five child who has had a diarrheal ilness in the past two weeks of at least 2 days duration. The aim is to identify 16 cases per cluster.

Within each site, random cluster selection will be repeated at the time of each new survey round. The sampling framework is summarized in figure 1.

CHILDREN UNDER FIVE YEARS OF AGE

Diarrheal Disease Episode in past 2 weeks and

at least 48 hrs duration

Dhaka Urban Municipalities Rural Upazillas

2 slum zones Khulna Abhoynagar

2 non-slum zones Camila Mirsarai

Sylhet Hobiganj

random random random

20 clusters 20 clusters 20 clusters

per zone per municipality per upazilla

at 16 casesper cluster

n=320 cases per site

N= 640 slum N=960 N=960

N= 640 non-slum urban municipal rural cases

per round per round per round

Figure 1. Summary of sampling frame for cluster surveys

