**Not applicable**

## Data Analysis

Describe plans for data analysis. Indicate whether data will be analyzed by the investigators themselves or by other professionals. Specify what statistical software packages will be used and if the study is blinded, when the code will be opened. For clinical trials, indicate if interim data analysis will be required to monitor further progress of the study.

The investigative team will carry out the data analysis. Data entry and general management will be done by the Data Resources and Surveillance Unit of the Division. Data will be entered and analyzed using SPSS version 12.0. Absolute counts, proportions and means with 95% confidence intervals were calculated. These and the regression analyses will be completed using STATA version 9, cluster survey program , that accounts for potential within cluster homogeneity. The analyses will stratified by location of residence into rural, municipal and city corporation households. The latter are further sub-grouped as predominantly slum or non-slum populations. For differences in categorical outcomes crude relative risks and 95% confidence intervals will determined. Multiple logistic regression models were tested for the prediction of health seeking behaviours and antibiotic, ORS or zinc treatments received. Of particular interest is the identification of disparities in health provider utilization, diarrhea treatment practices and illness expenditures by gender, asset quartile (household wealth) and geographic location of the household (rural, municipal or city corporation). The hypotheses to be tested are that significant (p<.05) differences in the management of childhood diarrhea favoring males, higher asset households and urban populations would be found.

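### Clusters are drawn without regard to size and a constant 16 cases per cluster is planned, so site coverage levels and the location comparison may be biased if zinc coverage varies with cluster caseload

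*Protocol*

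**What the plan says.** The Protocol sets the sampling scheme under Research Design and Methods.

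- **Rural.** Within "each sub-district we will randomly select 20 clusters based upon a listing of all wards in the subdistrict". The next sentence adds: "All wards will be enumerated and then randomly selected".
- **Municipal.** Twenty "clusters will be randomly selected within each municipality. Clusters are defined as geographic units".
- **Dhaka.** "Within each zone 20 clusters will be selected. Clusters are geographically defined"; these are population units taken from the latest census. Figure 1 labels the selection random for all three location types.
- **Take per cluster.** The text says "The aim is to identify 16 cases per cluster", following a household census of the cluster for any eligible child. Figure 1 gives "at 16 casesper cluster" and "n=320 cases per site". The Sample Size section uses 320 for every site.

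The Protocol does not mention selection proportional to size, cluster sizes, or a rule for what happens once 16 cases are found. Data Analysis names a Stata "cluster survey program , that accounts for potential within cluster homogeneity". Specific Aim 1 is the proportion of under-five diarrhoeal episodes that receive zinc, and H3 includes a comparison of that coverage between locations.

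**The concern.** Aim 1 concerns episodes, so each episode in a site should count equally. If clusters are drawn with equal chance and each contributes the same number of cases, each cluster counts equally instead, whatever its caseload. The estimate is then an average of cluster proportions. It differs from the proportion of episodes treated whenever coverage is related to caseload, for example if zinc supply or access to providers differs between dense and sparse wards.

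A correction for clustering cannot repair this, because it widens the interval without moving its centre. Most exposed are the coverage level at each site and the location comparison in H3, since the relation between caseload and coverage need not be the same in rural, municipal and city settings.

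The choice is made in the field. If interviewers stop at 16 and the cluster's full count is not kept, no later analysis can recover the weights.

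**Working it through.** **Inputs from the Protocol.** 20 clusters per site, 16 cases per cluster, design effect 2.0, 95% confidence, a margin of 5 points at 10% coverage, and 25% coverage assumed by the third cycle.

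**Inputs assumed here.** The Protocol gives no cluster sizes and no relation between size and coverage. I take the coefficient of variation (CV) of caseload as 0.3 to 0.8 and the correlation *r* between caseload and coverage as 0.3 to 0.5, with *r* = 0 for reference.

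**1. The plan's own figure.** n = 2 × 1.96² × 0.10 × 0.90 / 0.05² = 276.6. The stated 276 per site is reproduced.

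**2. Inclusion chance.** With M clusters in a site, C eligible cases in a cluster, equal-chance selection and 16 cases taken at random from the C, a case's chance is (20/M) × (16/C). Doubling C halves it. Selection proportional to caseload gives (20 × C/ΣC) × (16/C) = 320/ΣC, the same for every case.

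**3. Bias formula.** Unweighted estimate minus true episode proportion = −Cov(C, p)/mean(C) = −*r* × CV × SD, where p is cluster coverage and SD its between-cluster standard deviation.

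**4. SD implied by the design effect.** ICC = (2 − 1)/(16 − 1) = 0.067, and SD = √(ICC × P(1 − P)).
- P = 10%: √(0.067 × 0.09) = 7.7 points
- P = 25%: √(0.067 × 0.1875) = 11.2 points

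**5. Size of the bias (points, either sign), against the half-width at the same coverage.**

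| Coverage | r = 0 | CV 0.3, r 0.3 | CV 0.5, r 0.5 | CV 0.8, r 0.5 | Half-width, 320 cases |
|---|---|---|---|---|---|
| 10% | 0 | 0.7 | 1.9 | 3.1 | 4.6 (stated margin 5) |
| 25% | 0 | 1.0 | 2.8 | 4.5 | 6.7 |

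Half-width = 1.96 × √(2 × P(1 − P)/320).

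**6. Illustration.** Let half the wards have twice the cases of the others. With coverage 20% in small wards and 30% in large ones, the unweighted estimate is 25.0% and the true proportion (20 + 2 × 30)/3 = 26.7%. With the coverages reversed, the estimate is still 25.0% and the truth is (30 + 2 × 20)/3 = 23.3%.

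**7. Trends.** If the size pattern is stable, most of the bias cancels between rounds. At CV 0.5 and r 0.5, a rise from 10% to 25% coverage leaves 2.8 − 1.9 = 0.9 points.

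**The case against.** The strongest reply is that the fixed take is not firmly stated. Sixteen is worded as an aim, it stands beside a household census for any eligible child, and no stopping rule is given. If every case found were kept, equal-chance selection would be close to self-weighting and the problem would disappear. This stands as a real ambiguity, so a reader should not infer a strict quota of 16 as settled fact. Figure 1 and the uniform 320 per site favour the constant take, however, and under either reading the rule has to be stated.

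Second, random selection is not expressly called equal-probability, and the ward sentence covers rural sites only. Dhaka clusters are census-defined and may be of similar size. This also stands: rural wards and municipal units are the clear cases.

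Third, weights may appear in an analysis plan that is not at hand. Agreed, and their absence from the Protocol is not the point. The cluster draw, the take and the counts to be recorded are field decisions, and those belong in the Protocol.

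Fourth, many of the planned contrasts are partly protected. Gender and income comparisons are made within a location, and H1 and H2 follow the same sites over time. A shift common to both sides of such a contrast largely cancels. That is right, and it limits the concern mainly to coverage levels and the location part of H3.

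**Conclusion.** The concern holds in conditional form. As written, cases in high-caseload clusters have a lower chance of inclusion, and the stated correction does not address this. Site coverage levels and the location comparison may be biased, in either direction, by about 0.7 to 3.1 points at 10% coverage and 1.0 to 4.5 points at 25%. These figures rest on the Protocol's planning design effect, a constant take of 16, and assumed values of CV and *r*.

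Three stronger readings are not supported:

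- **That coverage is biased as a matter of fact.** The Protocol gives no cluster sizes and no relation between size and coverage. With no correlation the bias is zero.
- **That the bias can use up nearly the whole 5-point margin.** That sets 4.5 points, computed at 25% coverage, against a margin specified at 10%. Like for like, it is at most 3.1 against 5, or 4.5 against about 6.7.
- **That sites should also be weighted by population to form location totals.** The sites were chosen purposively for comparison with the baseline survey, and the prevalence sample sizes are set per site. Equal allocation is defensible, and weighting two or three purposive sites would not make a location representative.

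This is an inexpensive improvement worth making, not a defect that invalidates the survey.

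**What to change.** **Preferred.** Select the 20 clusters per site with probability proportional to census population, and state whether case-taking stops at 16 and how the 16 are chosen. The two rules must be set together: proportional selection is approximately self-weighting only with a constant take. It keeps 320 cases per site and a half-width of about 4.6 points at 10% coverage. The cost is obtaining population counts for the listed clusters. It is approximate because population stands in for caseload.

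**Alternative.** Keep the present random selection, complete the household census in every selected cluster even after 16 cases are found, record the eligible case count, and use inverse selection probabilities as weights in the Stata survey analysis. The cost is extra census work, one recorded variable and lost precision. Multiplying the variance by 1 + CV² (Kish, roughly an upper bound) gives, at 10% coverage:

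| CV of caseload | Half-width with 320 cases | Cases needed per site for 5 points |
|---|---|---|
| 0.3 | 4.9 | 302 |
| 0.5 | 5.2 | 346 |
| 0.8 | 6.0 | 454 |

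The planned 320 therefore meets the 5-point target at CV 0.3 but misses it at 0.5 and above, which favours the first option.
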